### Trial visits

A total of four trial visits will be conducted throughout the course of the trial. During the initial screening visit (visit 1), inclusion criteria and two out of four exclusion criteria will be evaluated. Once the patient has provided informed consent, the following patient characteristics are documented: basic demographic data, comorbidities, the modified frailty index (mFI), American Society of Anesthesiologists (ASA) and Eastern Cooperative Oncology Group (ECOG) scores, as well as tumour-specific parameters. Furthermore, patients are required to complete questionnaires assessing their preoperative quality of life. Quality of life will be evaluated using the aforementioned EORTC questionnaires, depending on the tumour localisation.

The second visit (visit 2) is scheduled for the day of surgery. Once the oesophagogastrostomy has been completed and none of the remaining two exclusion criteria (conversion and malfunction of the stapler) applies, the patient will be randomised using the REDCap randomisation tool. Intraoperative parameters will be collected, including incision-to-suture time, additional suture time for the anastomosis (study arm B), characteristics of the used stapler and intraoperative transfusions of packed red blood cells. Furthermore, the surgeon’s subjective intuition (subjective risk assessment) regarding four postoperative complications (anastomotic leak, conduit necrosis, chyle leak and recurrent laryngeal nerve injury/palsy) will be assessed.

The third and fourth study visits (visit 3 = 30 days postoperative and visit 4 = 6 months postoperative) may be conducted either as part of standard follow-up visits or by telephone. Visit 4 is considered to be part of the standard oncological follow-up. This encompasses a CT scan of the thorax and abdomen, in addition to an esophagogastroduodenoscopy, should clinical symptoms of dysphagia be observed. The primary and secondary endpoints, along with any serious adverse events (SAEs and AEs), will be evaluated and documented during each visit on the case report form (CRF). Data from patients with stapler malfunction, conversion to open surgery or inoperability will be documented until the time of the operation (visit 2). During visits 1 and 4, the standard blood tests (including haemoglobin concentration, leucocyte count and serum C-reactive protein) will be carried out and documented.

### Assessment of safety

Any adverse events (AEs) and serious adverse events (SAEs) that occur during the course of the study will be documented. AE is defined as any event that deviates from the norm of the perioperative course of a robot-assisted oesophagectomy. SAE is defined as any event that can occur at any time during the study and either leads to death, threatens the patient’s life, results in persistent or significant impairment or disability of the patient. SAEs must be reported to the principal investigator within 24 h. The principal investigator is responsible for notifying the responsible ethics committee, if SAEs occur.

Automated blinded reports of the REDCap online database platform, including the secondary safety endpoint (CDC grade ≥ 3b), will be available to the steering committee on a continuous basis. These reports will be subject to monthly review and help to detect any unexpected increase in postoperative risk associated with the intervention. In case of imbalances between groups, additional safety review may be initiated. The study may be terminated prematurely by the steering committee or the responsible ethics committee in the following cases: in the event of medical or ethical concerns that preclude the continuation of the study (e.g. secondary safety endpoint or SAEs indicating a potential health risk associated with study participation), inadequate patient recruitment or the emergence of external evidence suggesting the termination of the study.

### Statistics

#### Statistical considerations

All analyses will be performed on an intention-to-treat basis, which comprises all patients randomised with successful RAMIE. Discrete endpoints including the primary endpoint will be described with the use of frequencies and percentages with 95% confidence intervals and will be compared by the chi-square test or Fisher’s exact test. Although randomisation is expected to balance baseline characteristics, additional multivariate analysis will be performed for variables affecting binomial endpoints to control for potential residual confounding. This analysis will use a multivariable logistic regression model including clinically relevant covariates that may influence anastomotic healing. These variables include, but are not limited to age, body mass index (BMI), tumour histology, neoadjuvant treatment and stapler diameter. Adjusted odds ratios (ORs) with 95% confidence intervals will be reported.

Continuous outcomes such as incision-to-suture time will be compared between groups using either Student’s *t*-test (if normally distributed) or the Mann–Whitney *U* test (if skewed). Ordinal outcomes, such as the Clavien–Dindo complication grading, will be analysed with non-parametric tests like the Mann–Whitney *U* test.

Quality-of-life scores obtained from the EORTC QLQ-C30, QLQ-OES18 and QLQ-OG25 questionnaires at baseline and 6 months postoperatively will be assessed using repeated measures analysis, such as mixed-effects linear models, to account for within-subject correlation over time. For any time-to-event outcomes (e.g. time to readmission or death), Kaplan–Meier survival analysis and the log-rank test will be applied, and, if appropriate, a Cox proportional hazards model will be used to estimate hazard ratios with 95% confidence intervals.

All statistical tests will be two-sided, with a significance level set at *α* = 0.05. Sensitivity analyses will be performed using the per-protocol population. All analyses will be fully specified in a statistical analysis plan that is written prior to database closure.

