#### Withdrawal criteria

Patients may withdraw from the trial at any time without providing justification. Exclusion from the trial will occur in cases where RAMIE is not performed, for instance, due to technical irresectability, conversion to conventional resection or metastatic disease. However, the withdrawal and reasons will be documented in the patient file and the CRF (case report form), and a CONSORT flow diagram will be provided to ensure comprehensive transparency.

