### Interventions

#### Surgical technique

To preclude the potential for learning-associated bias, surgeons with the requisite proficiency will be permitted to perform the randomised interventions. Surgeons participating in the trial as the responsible surgeons must have a minimum of 20 RAMIEs of personal operative experience. This threshold is based on the lower variance range of the learning curves for RAMIE, as determined in a recent systematic review [14]. It should be noted that the standard technique and surgical instruments may vary in several aspects. Nevertheless, the following guidelines have been defined for the present study to reduce the impact of performance bias:The abdominal and thoracic parts of the procedure are performed robotically.A circular, end-to-side oesophagogastrostomy is performed after gastric tube pull-up via a muscle-sparing mini-thoracotomy.A circular stapler with a size range of 25–29 mm is employed.The gastric conduit stump is closed with a linear stapler, with the shortest distance between the linear and circular stapler lines being at least 1 cm.Randomisation is conducted intraoperatively, after the completion of the oesophagogastrostomy.The circumferential suture reinforcement (study arm B) may be performed in an interrupted or continuous fashion with resorbable material (e.g. PDS 4–0, V-loc 4–0). Any type of surgical stitching technique or suture pattern is allowed, provided that the entire circular stapler line is addressed. In case of interrupted suture technique, the number of sutures required is dependent upon the size of the anastomosis.No additional measures to reinforce the anastomosis (e.g. omental flap, pleural flap) are permitted.The placement of drains is at the surgeon’s discretion.Patients do not receive a gastric tube.Perioperative complications associated with oesophagectomy are treated according to current best practices and clinical standards.

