### Assignment and randomisation

Patients who have been screened and deemed eligible will be included in the trial following the provision of written informed consent. Randomisation will be conducted intraoperatively, after the completion of the oesophagogastrostomy and verification of the exclusion criteria. The randomisation lists were generated by block randomisation (block size 10) by a computer-based random number generator using the R statistical package (version 4.4.1). The lists were incorporated into the REDCap randomisation tool. The randomisation process will be conducted by authorised trial personnel using the electronic REDCap system.

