#### Blinding

The STITCHES trial is a double-blind study. As it is not feasible to blind the surgeon, the patients and the follow-up investigators are blinded. The case report forms, which can be viewed by the follow-up investigators, do not specify which study arm the patients belong to. To ensure impartiality, the postoperative study visits are not carried out by the surgeon.

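### The set labelled intention-to-treat adds an undefined success condition, so a randomised patient converted later in the operation would be dropped and have no leak outcome recorded

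*Protocol article*

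**What the plan says.** All references are to the protocol article.

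- **Analysis set** (Statistical considerations): "All analyses will be performed on an intention-to-treat basis, which comprises all patients randomised with successful RAMIE". This covers every analysis, including the primary endpoint. Success is not defined. The only sensitivity population named is per-protocol.
- **Timing** (Assignment and randomisation): "Randomisation will be conducted intraoperatively, after the completion of the oesophagogastrostomy and verification of the exclusion criteria". Trial visits repeats this as a condition: if "none of the remaining two exclusion criteria (conversion and malfunction of the stapler) applies, the patient will be randomised".
- **Exclusion** (Withdrawal criteria): "Exclusion from the trial will occur in cases where RAMIE is not performed, for instance, due to technical irresectability, conversion to conventional resection". Metastatic disease is a further example. Withdrawals and their reasons are to be documented and shown in a CONSORT diagram.
- **Data stop** (Trial visits): "Data from patients with stapler malfunction, conversion to open surgery or inoperability will be documented until the time of the operation (visit 2", visit 2 being the day of surgery.
- **After randomisation** (Surgical technique): "The circumferential suture reinforcement (study arm B) may be performed in an interrupted or continuous fashion with resorbable material", and the whole circular stapler line has to be covered. Arm A has no corresponding step.
- **Blinding** (Blinding): "As it is not feasible to blind the surgeon, the patients and the follow-up investigators are blinded".

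**The concern.** An intention-to-treat set is fixed by randomisation alone. This one has a second condition, which nothing ties to the time before allocation. The surgeon knows the arm for the rest of the operation, and the text does not say who judges success, when, or by what criterion.

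The exclusion and data-stop rules make this more than a matter of labelling. Read literally, they would also apply to a patient converted after randomisation, so the patient would be left out of the analysis and the plan would collect no leak outcome for that patient at visits 3 and 4. The per-protocol sensitivity analysis does not bring such patients back.

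What is at stake is the comparability of the arms on the primary endpoint. Further work on the anastomosis after randomisation happens only in arm B, so post-randomisation losses need not be balanced.

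**Working it through.** **Step 1. When can each ground for removal occur?**

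| Ground | Can it arise after randomisation? |
|---|---|
| Technical irresectability, inoperability | No: the resection and anastomosis are already complete |
| Metastatic disease as a reason for not performing RAMIE | No, for the same reason |
| Stapler malfunction at the oesophagogastrostomy | No: checked before randomisation |
| Conversion to open surgery | Mostly before, and checked then; still possible between randomisation and the end of surgery |
| RAMIE not successful (undefined) | Cannot be decided from the text |

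The affected group is therefore patients converted after randomisation, plus anyone removed under the undefined success condition. The documents give no rate for either.

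**Step 2. The plan's own sample size.** Inputs from Sample size calculation: 17% and 11%, two-sided alpha 0.05, 80% power, chi-squared test. With mean rate 0.14 and pooled variance:

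n = [1.96 × √(2 × 0.14 × 0.86) + 0.8416 × √(0.17 × 0.83 + 0.11 × 0.89)]² / 0.06²
= (0.9618 + 0.4115)² / 0.0036 ≈ 524 per arm.

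The stated figure of about 525 is reproduced. It contains no allowance for exclusions after randomisation, so it says nothing about how many are expected.

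**Step 3. Effect of removals on the arm B rate.** Let f be the share of arm B removed after randomisation and r the leak risk in those removed. Assume no true effect (17% in both arms) and no removals from arm A. Both f and r are assumptions.

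Observed arm B rate = (0.17 − f × r) / (1 − f)

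For example, f = 2% and r = 50% gives (0.17 − 0.01) / 0.98 = 16.3%, a shift of −0.7 points.

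| f | r = 50% | r = 30% | r = 17% | r = 5% |
|---|---|---|---|---|
| 1% | −0.3 | −0.1 | 0 | +0.1 |
| 2% | −0.7 | −0.3 | 0 | +0.2 |
| 5% | −1.7 | −0.7 | 0 | +0.6 |

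Entries are shifts in the arm B leak rate in percentage points; a negative value flatters reinforcement. The sign depends only on whether r lies above or below 17%.

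**Step 4. Effect on the test.** At 525 per arm, by normal approximation and with f = 2%, the chance of a false finding in favour of reinforcement is 4.8% at r = 50%, 2.5% (nominal) at r = 17% and about 2.0% at r = 5%. With f = 1% and r = 50% it is 3.5%.

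**Step 5. Interim look.** Continuation requires an absolute difference of at least 1%. Suppose 8/50 in each arm, a difference of zero.

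- Remove one arm B patient who leaked: 8/50 against 7/49, that is 16.0% − 14.3% = 1.7 points. The threshold is crossed.
- Remove one arm B patient who did not leak: 8/50 against 8/49, that is 16.0% − 16.3% = −0.3 points. It is not crossed.

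One exclusion can change the continuation decision at 50 per arm, but whether it does depends on that patient's outcome.

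**The case against.** The strongest defence is that the extra words do nothing. Randomisation comes after the anastomosis is finished and after conversion and stapler malfunction have been ruled out, so a randomised patient has already had the robotic resection and reconstruction, and the success wording may simply describe that population. Most grounds listed under Withdrawal criteria and in the data-stop sentence can arise only earlier. This stands as far as numbers go: few patients are likely to be affected. It does not rescue the wording. If the condition removes nobody, it can be deleted without loss; if it removes anybody, the set is not intention-to-treat. Conversion after randomisation remains possible, and neither rule exempts it.

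A reader might go further and infer that the plan biases the trial towards reinforcement. The documents do not support that. Nothing in them removes a patient for tissue tearing or for a redone anastomosis; conversion is the only named ground that can arise late. The leak risk of those removed is unknown, and below 17% the shift runs against reinforcement. A shift of 1.7 points needs 5% of arm B lost, nobody lost from arm A and a 50% leak risk, none of which is documented.

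Nor is the loss shown to be irreparable. Visit 4 belongs to standard oncological follow-up, so leak status may be retrievable from routine records, and the CONSORT diagram would make the losses visible. The Documentation section also extends eCRF entry to excluded persons, though it does not lift the visit-2 limit.

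Finally, the article defers full specification to a statistical analysis plan written before database closure. That plan could redefine the set, but it would not by itself restart data collection that the trial rules had ended.

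**Conclusion.** The point holds as a defect in the stated definition and in the scope of two rules. As written, a randomised patient converted before the end of surgery would drop out of every analysis and have no leak outcome collected under the plan, and the named sensitivity analysis would not restore that patient. Because the added anastomotic step exists only in arm B and the surgeon is unblinded, such losses could differ by arm.

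The size is probably small, and the direction is not established. With 17% leakage in both arms and 2% of arm B removed, the shift runs from about −0.7 points (leak risk 50%) to +0.2 points (leak risk 5%), against a design effect of 6 points. These figures rest on assumed removal shares and leak risks, and on no removals from arm A. The case for changing the text is that it concerns the primary comparison, recruitment has begun and the correction costs almost nothing; it does not depend on a large expected bias.

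**What to change.** 1. **Statistical considerations:** define the primary set as all randomised patients, analysed in the arm to which they were allocated, whatever happens after randomisation.
2. **Withdrawal criteria:** state that the exclusions for RAMIE not being performed apply only to patients who have not been randomised.
3. **Trial visits:** limit the visit-2 data stop in the same way, and collect the primary and secondary endpoints to visit 4 for everyone randomised, except where consent is withdrawn.
4. **Per-protocol set:** use successful RAMIE only here, with a definition.

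If any randomised patient has already been excluded under the current wording, seek that patient's leak status from routine records where consent allows.

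The cost is an amendment to the wording in these sections and follow-up of a few patients. The calculation of about 525 per arm need not change on this account.

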#### Secondary endpoints

Secondary endpoints include incision-to-suture time, duration of circumferential suture reinforcement, anastomotic stenosis rate, postoperative morbidity and mortality according to the Clavien–Dindo classification (CDC), and quality of life. Perioperative complications associated with oesophagectomy are recorded in accordance with the ECCG definitions.

Postoperative morbidity with CDC grade ≥ 3b will be the secondary safety endpoint. Quality of life (QoL) is assessed using the EORTC QLQ-C30, EORTC QLQ-OES18 and EORTC QLQ-OG25 questionnaires [1, 3, 9], provided by the European Organisation for Research and Treatment of Cancer.

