#### Data collection

To achieve study results that are comparable to those of other trials regarding oesophagectomy, the assessment of postoperative morbidity in the STITCHES trial is based on the recommendations of the Esophagectomy Complication Consensus Group (ECCG) [8]. During each study visit, all parameters of interest, including primary and secondary endpoints and AEs/SAEs, are evaluated and documented in accordance with the standardised eCRF.

Visit 1: The following patient characteristics are documented: basic demographic data (age, sex, height, weight and BMI), mFI, ASA and ECOG scores, as well as tumour-specific parameters (tumour type and location, TNM classification, and the prevalence and type of neoadjuvant treatment). A preoperative blood test is conducted including serum albumin, creatinine, haemoglobin, leukocytes, CRP, vitamin B12, vitamin D3 and tumour markers CA 19–9 and CEA. Furthermore, each patient is required to complete the EORTC QoL questionnaires.

Visit 2: On the day of surgery, the incision-to-suture time, duration of additional suture of the anastomosis (if randomised to study arm B), type of stapler (manufacturer, diameter, powered stapler, yes or no) and the number of intraoperative blood transfusions are recorded.

To document the duration of suture reinforcement of the stapled anastomosis, the timer is started with the initial stitch and stopped with the cutting of the suture. Furthermore, a subjective risk assessment is conducted by the surgeon regarding four postoperative complications: anastomotic leak, conduit necrosis, chyle leak and recurrent laryngeal nerve injury/palsy.

Visit 3: This study visit encompasses possible postoperative mortality and morbidity, the necessity for blood transfusions, the date of discharge and the occurrence of readmission to the hospital. The discharge information comprises the location of discharge, whether at home or to a further medical facility. Morbidity is evaluated and documented in accordance with the ECCG criteria and graded according to Clavien–Dindo.

Visit 4: This study visit includes all parameters of visit 3. Furthermore, an oncological follow-up (suspected and/or confirmed relapse), as well as a routine blood test and an assessment of quality-of-life following surgery (corresponding to visit 1) are required.

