#### Documentation

It is the responsibility of the investigator to ensure that the study is conducted in accordance with the professional code for physicians, the Declaration of Helsinki in its current version and the study protocol. A sound documentation of the data is mandatory. All data collected in this study must be entered into the eCRF by appropriately authorised persons. This also applies to data from persons who have been excluded from the study. The study site records participation on a patient identification list. This list is utilised for the identification of participating individuals and comprises the patient number, full name, date of birth and date of admission to the STITCHES trial. The patient identification list remains at the trial centre after the study is completed.

The audit trial functionality within the REDCap online database automatically logs all data and associated corrections with the date, time and the individual responsible for the entry. This enables the retrieval of previous entries at any time. Records and documents related to the STITCHES trial must be retained by the investigator for 10 years in accordance with Good Clinical Practice.

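### Incision-to-suture time is compared without adjusting for operating time that precedes randomisation, which costs precision but causes no bias

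*Protocol article*

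**What the plan says.** Two time measures are listed in the protocol article under Secondary endpoints: "Secondary endpoints include incision-to-suture time, duration of circumferential suture reinforcement, anastomotic stenosis rate". The first is compared between arms. Under Statistical considerations, "Continuous outcomes such as incision-to-suture time will be compared between groups using either" Student's t-test or the Mann–Whitney U test, depending on the distribution. Covariate adjustment is described there only for binary outcomes: "additional multivariate analysis will be performed for variables affecting binomial endpoints to control for potential residual confounding". Full specification is left to a statistical analysis plan (SAP), which is not shown.

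The second measure exists only in arm B. According to Data collection, "the timer is started with the initial stitch and stopped with the cutting of the suture".

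On the order of events, Assignment and randomisation says: "Randomisation will be conducted intraoperatively, after the completion of the oesophagogastrostomy and verification of the exclusion criteria". The Surgical technique section agrees ("Randomisation is conducted intraoperatively, after the completion of the oesophagogastrostomy") and adds: "The abdominal and thoracic parts of the procedure are performed robotically". The Documentation section says that the REDCap audit function "automatically logs all data and associated corrections with the date, time", together with the person who made the entry.

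**The concern.** Total operating time is the sum of a part before randomisation and a part after it. Allocation can change only the second. The first covers the work up to and including the stapled anastomosis, and differences between patients in that work enter the comparison as noise. A two-sample test on the total carries all of this noise, although the time before randomisation is a baseline quantity that could be adjusted for.

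At stake is how precisely the trial can say how many minutes reinforcement adds to the operation. With a wide interval, a real added time could be reported as no significant difference. The primary endpoint and the sample size are not affected.

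**Working it through.** **The plan's own figure.** The article gives no planning figure for operating time. Its sample size for the leak rate (17% against 11%, two-sided 0.05, 80% power) can be reproduced. With a pooled rate of 0.14, n = [1.960·√(2·0.14·0.86) + 0.842·√(0.17·0.83 + 0.11·0.89)]² / 0.06² ≈ 524 per arm, against about 525 stated. So 525 per arm is used below as the planning size, and 50 per arm as the first stage.

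**Same target.** Write total time as Y = X + P, with X from incision to randomisation and P from randomisation to closure. Randomisation balances X in expectation, so the expected arm difference in Y equals that in P. The unadjusted test is therefore unbiased, and both alternatives estimate the same number of minutes.

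**Precision.** The standard error (SE) of the arm difference is SD·√(2/n).
- Unadjusted: SD is the SD of Y.
- Comparing P directly: SD is the SD of P.
- ANCOVA on X: the residual SD is SD(P)·√(1 − ρ²), where ρ is the correlation of X and P. In large samples this is never worse than comparing P.

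**Assumptions.** The documents give no SD, no durations and no expected suturing time. Take SD(Y) = 60 min. If X and P are uncorrelated and a share f of the variance arises before randomisation, SD(P) = 60·√(1 − f). An SD(P) of 20 min means f = 1 − 400/3600 = 0.89, a favourable case, so smaller shares are shown too.

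| | Unadjusted (SD 60) | f = 0.5 (SD 42.4) | f = 0.8 (SD 26.8) | f = 0.89 (SD 20) |
|---|---|---|---|---|
| SE, 50 per arm (min) | 12.0 | 8.5 | 5.4 | 4.0 |
| SE, 525 per arm (min) | 3.7 | 2.6 | 1.7 | 1.2 |

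**Power.** Power ≈ Φ(Δ/SE − 1.96), where Δ is the assumed true added time. For example, 15 min at 50 per arm unadjusted gives Φ(15/12.0 − 1.96) = Φ(−0.71) = 24%.

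| Per arm, Δ | Unadjusted | f = 0.5 | f = 0.8 | f = 0.89 |
|---|---|---|---|---|
| 50, 10 min | 13% | 22% | 46% | 71% |
| 50, 15 min | 24% | 42% | 80% | 96% |
| 525, 5 min | 27% | 48% | 86% | 98% |
| 525, 10 min | 77% | 97% | >99% | >99% |
| 525, 15 min | 98% | >99% | >99% | >99% |

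**Range.** For a total SD of 40 to 80 min, the unadjusted SE at 50 per arm is 8 to 16 min, against 4 min if SD(P) is 20. For a total SD of 45 to 90 min, the difference detectable unadjusted with 80% power (2.80·SE) is 25 to 50 min at 50 per arm, 8 to 16 min at 525 and 6 to 11 min at 1000.

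**The case against.** The strongest case against the point has four parts.

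- **The cost is measured directly.** A reader might infer that the planned comparison hides the time cost of reinforcement. The documents do not support that: the duration of reinforcement is its own secondary endpoint, timed in arm B and free of dissection time. This stands and limits the point. But the timer has no control value, and it omits set-up before the first stitch and any effect on later steps. Of the listed endpoints, only incision-to-suture time gives a between-arm estimate of the whole cost.
- **The planned test is valid.** This stands in full. Only efficiency is at issue, on one secondary endpoint.
- **It is detail for the SAP.** This stands in part. The SAP may add adjustment, but the article names this endpoint and its tests and describes adjustment for binary outcomes only. The point concerns that stated choice.
- **The numbers are assumed, and the data may not exist.** Both are fair. Every SD is an assumption. Arm B allows any stitching pattern, which could raise the variance after randomisation and shrink the gain. The audit trail supports a logged randomisation time, but no clock time of incision or closure is among the listed data items. A reader should not conclude that the covariate is already held for every patient.

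**Conclusion.** The point holds as a cheap improvement of minor weight. The order of steps in the article shows that time before randomisation is inside the endpoint and cannot depend on the arm. That this part is the larger one is a sound inference from the surgical sequence, but no durations are given to confirm it.

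Under the assumed SDs of 60 and 20 min, the standard error is three times as large as it need be; with half the variance before randomisation, it is about 1.4 times (12.0/8.5). The consequence depends on sample size. At about 525 per arm the unadjusted test would usually detect 15 added minutes (98% power at SD 60, 77% at SD 90). It is weak if the trial ends after the first 100 patients, which the interim rules allow, or if the added time is short.

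**What to change.** State in the SAP that incision-to-suture time will be analysed by ANCOVA with arm as the factor and incision-to-randomisation time as covariate, reporting the adjusted mean difference in minutes with its 95% confidence interval. Comparing randomisation-to-suture time between arms is an acceptable alternative. Robust standard errors would deal with skewness and keep the result in minutes. The arm B stitching time should be reported alongside as a descriptive measure.

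Take the time of randomisation from REDCap. Confirm that the clock time of incision is recorded, or add it; the second option also needs the clock time of closure. Since the total incision-to-suture time is already collected, either clock time yields the other, so one added field is enough. The cost is that field, filled retrospectively for patients enrolled since November 2024, and a sentence or two in the SAP.
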